## Abstract

**Background:**

Obesity is characterized by increased fat mass and is associated with the development of insulin resistance syndrome (IRS), usually known as metabolic syndrome. The alteration of the intestinal microbiota composition has a role in the development of IRS associated with obesity, and probiotics, which are live microorganisms that confer a health benefit to the host, contribute to restore intestinal microbiota homeostasis and lower peripheral tissue insulin resistance. We aim to evaluate the effects of the probiotic strain *Lactobacillus reuteri* (*L. reuteri)* V3401 on the composition of intestinal microbiota, markers of insulin resistance and biomarkers of inflammation, cardiovascular risk, and hepatic steatosis in patients with overweight and obesity exhibiting IRS.

**Methods/design:**

We describe a randomized, double-blind, crossover, placebo-controlled, and single-centre trial. Sixty participants (aged 18 to 65 years) diagnosed with IRS will be randomized in a 1:1 ratio to receive either a daily dose of placebo or 5 × 10^9^ colony-forming units of *L. reuteri* V3401. The study will consist of two intervention periods of 12 weeks separated by a washout period of 6 weeks and preceded by another washout period of 2 weeks. The primary outcome will be the change in plasma lipopolysaccharide (LPS) levels at 12 weeks. Secondary outcomes will include anthropometric parameters, lipid profile, glucose metabolism, microbiota composition, hepatic steatosis, and inflammatory and cardiovascular biomarkers. Blood and stool samples will be collected at baseline, at the midpoint (only stool samples) and immediately after each intervention period. Luminex technology will be used to measure interleukins. For statistical analysis, a mixed ANOVA model will be employed to calculate changes in the outcome variables.

**Discussion:**

This is the first time that *L. reuteri* V3401 will be evaluated in patients with IRS. Therefore, this study will provide valuable scientific information about the effects of this strain in metabolic syndrome patients.

**Trial registration:**

The trial has been retrospectively registered in ClinicalTrials.gov on the 23rd November 2016 (ID: NCT02972567), during the recruitment phase.

**Electronic supplementary material:**

The online version of this article (10.1186/s12906-018-2371-x) contains supplementary material, which is available to authorized users.

## Trial status

Currently, the trial is ongoing and the analyses of the data and biomarkers continuing.

## Background

Obesity is a chronic, low-grade systemic inflammatory disease that is complex and multifactorial, with both genetic and environmental factors involved. This condition and its comorbidities have reached epidemic proportions, both in developed and developing countries [1]. Obesity is associated with the development of insulin resistance syndrome (IRS), commonly referred to as metabolic syndrome. IRS is defined by the presence of impaired glucose metabolism, hypertriglyceridemia, low concentrations of serum high-density lipoprotein (HDL) and other alterations associated with an increased risk of cardiovascular disease (CVD). IRS is a key factor in the development of type 2 diabetes mellitus (DM2), CVD and non-alcoholic fatty liver disease (NAFLD) [2]. Clinical management of IRS remains a public health challenge. Indeed, current treatment is based on changes in lifestyle through hygienic-dietary measures (diet and exercise) combined with medical therapy, if necessary, to treat the components of IRS separately and not as a whole entity.

In recent years, it has become clear that the alteration of the intestinal microbiota composition can contribute to the development of insulin resistance associated with obesity [3–5]. In this sense, a decreased *Bacteroidetes*/*Firmicutes* ratio has been described in obese compared to lean individuals [6]. Furthermore, an aberrant intestinal microbiota is able to promote a state of low-grade systemic inflammation, insulin resistance and increased CVD risk through mechanisms that include exposure to bacterial products. In particular, lipopolysaccharide (LPS) produces metabolic endotoxaemia capable of modulating pro-inflammatory cytokines and altering glucose and lipid metabolism in the liver and adipose tissue [7, 8]. In addition, it has been reported that high concentrations of serum LPS-binding protein (LBP) are associated with obesity, IRS and DM2 [9].

Probiotics are live microorganisms that confer a health benefit on the host when administered in adequate amounts. They can modulate the gut microbiota and the immune system. The strains most frequently used as probiotics belong to the *Bifidobacterium* and *Lactobacillus* genera [10]. In this regard, our group has reported that the administration of 9 × 10^9^ cfu (colony-forming units)/day of three probiotics strains (*Lactobacillus paracasei* CNCM I-4034, *Lactobacillus rhamnosus* CNCM I-4036 and *Bifidobacterium* breve CNCM I-4035) to healthy subjects during 30 days induced significant colon microbiota modifications [11].

This fact opens the possibility of a new approach in the treatment of IRS, not with drugs but with functional foods containing probiotics [12]. Intervention studies to determine the effect of probiotics on the components of IRS are limited and often contradictory, mainly due to differences in the design of the study protocol and in the selection of the probiotic strain because the effects observed are strain dependent.

In this sense, it has been described that *Lactobacillus reuteri (L. reuteri)* V3401 (CECT 8605) successfully reduces the absorption of cholesterol by intestinal epithelial cells in in vitro and in vivo assays. This cholesterol-absorbing capacity may be induced through an increase in lytic activity specific to *L. reuteri* V3401 [13]. In an animal model, mice fed a hypercholesterolemic diet supplemented with 2 × 10^9^ cfu of *L. reuteri* V3401/day for 57 days exhibited reduced serum cholesterol levels compared to hypercholesterolemic mice that did not receive the probiotic supplement. Moreover, the animals supplemented with the probiotic strain showed glycemic values similar to those of normocholesterolemic mice [13]. These results suggest that this strain might be adequate for the treatment of dyslipidaemia [13]. We therefore hypothesize that *L. reuteri* V3401 may provide a beneficial effect on IRS treatment, and we aim to study *L. reuteri* V3401 effects in a crossover clinical double-blind, randomized, placebo-controlled trial in IRS patients.

## Method/design

### Aim of the study

The main objective is to evaluate the effects of *L. reuteri* V3401 on the composition of intestinal microbiota, anthropometric parameters, and biomarkers of insulin resistance (inflammation, cardiovascular risk, and hepatic steatosis) in IRS patients.

### *Lactobacillus reuteri* V3401 characteristics

Lyophilized *L. reuteri* V3401 capsules will be specially prepared for the trial. The capsules will contain 5 × 10^9^ cfu, in agreement with previous data obtained from studies in animals [13]. The placebo will contain maltodextrin and will also be supplied in capsules. Capsules for the probiotic and placebo will be indistinguishable in shape, colour, and organoleptic conditions, and will be provided by Biosearch Life.

### Study design

The study is a randomized, double-blind, crossover, controlled, and single-center trial. The trial will be conducted by members of both the Endocrinology and Nutrition Department and the Gastroenterology Department of Complejo Hospitalario de Jaén (Spain). Participants will be instructed to follow a prebiotic- and probiotic-free diet two weeks before the beginning of the intervention and during the study. The study will be performed as shown in Fig. 1. Blood samples, as well as the food and physical activity questionnaire will be analysed by the members of the University of Granada at the University facilities. Microbial DNA isolated from faecal samples will be sequenced in the facilities of the Hospital Universitario San Cecilio (Granada, Spain).

**Fig. 1 Fig1:**
[figure not shown]
Flow-chart of the study

The protocol (PROSIR version 2) will be approved by the local Ethics Committee of Granada and Jaen (CEI-Granada and CEI Jaén with references CEI- Jaen 25,022,016 and CEI-Granada 28,022,016, respectively), and conducted according to the standards given in the Declaration of Helsinki and the Good Clinical Practice Guidelines [14]. All investigators participating in the trial are appropriately qualified.

The Standard Protocol Items: Recommendations for Interventional Trials (SPIRIT) guidelines for this study protocol has been included as an Additional file 1.

### Participants, interventions, and outcomes

#### Inclusion criteria

Individuals aged 18 to 65 years newly-diagnosed with IRS, according to the criteria of the International Diabetes Federation (IDF), and without any previous treatment for the metabolic syndrome, will participate in the study. The prescription of any treatment not allowed during the course of the study, according to exclusion criteria, will be considered a reason for dropping out. Before starting the trial, written informed consent will be provided by all patients.

#### Exclusion criteria

The use of hypoglycaemic treatment, lipid-lowering medications and treatment with drugs that increase liver enzymes, treatment with specific anti-hypertensives (beta-blockers, angiotensin 2 receptor antagonists, angiotensin-converting enzyme inhibitors) will be considered as an exclusion criteria. Moreover, the exclusion criteria include the presence of kidney disease; diabetes; acute liver injury or severe cirrhosis; immune deficiency conditions; elevated values of C-reactive protein; pregnancy or breastfeeding; history of drug or alcohol abuse; or participation in a study of an investigational medication within the past 30 days.

### Recruitment

A total of 60 subjects are expected to be recruited from the Endocrine and Nutrition Clinic at Complejo Hospitalario de Jaén (Spain) by the physician responsible, through the local newspaper and using advertisement posts at different locations at the hospital facilities.

### Randomization, allocation, and blinding

Patients will be randomly allocated in a 1:1 ratio to receive a capsule containing either lyophilized *L. reuteri* V3401 or placebo once daily with food for 12 weeks. A stratified block-randomization method of a software program for sequence generation will be used. After a 6-week washout, participants will crossover to receive the alternative intervention for another 12 weeks. Subjects and investigators will be blinded to the treatment allocation during the course of the intervention. The blind will be broken following consultation with the sponsor.

The capsules will be prepared in special containers with the random number label. Capsules will be delivered at the beginning of each intervention and six weeks later to ensure probiotic viability.

### Intervention

We will conduct a standard semi-structured clinical interview with clinical assessment. Subsequently, we will audit the clinical reports to extract relevant information (Additional file 2). In addition, a physical examination, and a complete blood test will be also conducted prior to inclusion in the study. Participants meeting the inclusion criteria will be randomly assigned to the probiotic or placebo group. During the intervention, participants will be asked to ingest a capsule per day with food. Capsules will be administered over two periods of 12 weeks. During the washout period, participants will not receive dietary recommendations. Clinical follow-up visits will be scheduled at the beginning, midpoint, and end of each interventional period. At each visit, anthropometric parameters will be registered, and possible adverse effects will be recorded (Table 1).

**Table 1 Tab1:** Detailed study procedures

Visits (V) Week (W)			V1 (W-2)	V2 (W0)	V3 (W6)	V4 (W12)	Washout	V5 (W18)	V6 (W24)	V7 (W30)
Screening analysis			X							
Demographics/ general information			X							
Informed content form			X							
Randomization and allocation			X							
Treatment distribution			X							
Blood test				X		X		X		X
Stools collection				X	X	X		X	X	X
Hepatic ultrasound				X		X				X
Assessments	General outcomes									
		Clinical interview		X	X	X		X	X	X
		Blood pressure and anthropometry		X	X	X		X	X	X
		3-day dietary record		X		X		X		X
		Food Frequency Questionnaire (FFQ)		X		X		X		X
		Physical activity questionnaire (IPAQ)		X		X		X		X
	Primary outcomes									
		Plasma LPS		X		X		X		X
	Secondary outcomes									
		Blood Pressure		X	X	X		X	X	X
		HOMA		X		X		X		X
		Lipid profile		X		X		X		X
		Inflammatory markers		X		X		X		X
		Hepatic steatosis markers		X		X		X		X

The data and samples will be collected in the Complejo Hospitalario de Jaén by qualified personal, and will be codified according to the biobank of the Public Health System of Andalusia (BSSPA) guidelines. All samples will be managed and processed in accordance with BSSPA protocols. All samples will be centralized at the BSSPA facilities.

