### Dietary and physical activity control

Participants will be provided with a list of local foods to avoid due to their potential probiotic or prebiotic content. Subjects will be asked to complete a three-day dietary record at the beginning, midpoint, and end of each intervention period. Energy and dietary intakes will be assessed from the 3-day records using the EvalFINUT software (http://www.finut.org/evalfinut/). Additionally, subjects will complete the Food Frequency Questionnaire (FFQ) at the beginning of each intervention period. Participants will receive nutritional counselling on a healthy Mediterranean diet providing approximately 25 kcal/kg/ day to achieve and maintain 7% loss of initial body weight and increase moderate-intensity physical activity (such as brisk walking) for at least 150 min/week following the guidelines of the American Diabetes Association for the prevention or delay of DM2 [15]. Likewise, physical activity will be monitored through the International Physical Activity Questionnaire (IPAQ) at the beginning, midpoint, and end of each intervention period. In the following visits, an intensive lifestyle intervention programme will be carried out to reinforce the behaviour.

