### Outcome measures

Clinical and anthropometric parameters (weight, height, waist circumference and blood pressure) will be recorded. A hepatic ultrasound (US) test will also be performed at the beginning of the two intervention periods, as well as at the end of the intervention periods. US diagnostic criteria for diagnosis and grading of hepatic steatosis will be used [16]. Smoking habits and anxiolytic and antihistaminic drug intake will also be recorded.

Blood samples will be collected after 12 h of fasting at the beginning and at the end of each intervention period (t0, t12, t18 and t30). Stool samples will also be taken at baseline and at 6, 12, 18, 24, and 30 weeks (t0, t6, t12, t18, t24, and t30, respectively). Serum will be collected by centrifugation of blood samples for the determination of biochemical and inflammation biomarkers. Faecal samples will be collected and kept at − 80 °C until analysis. All samples will remain frozen at − 80 °C in the BSSPA Platform.

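### The protocol gives conflicting dietary instructions for the week 12–18 washout, so the conditions before the week 18 baseline are not defined

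*Protocol article*

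**What the plan says.** Four places in the protocol article bear on diet around the two period baselines.

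- **Study design:** "Participants will be instructed to follow a prebiotic- and probiotic-free diet two weeks before the beginning of the intervention and during the study". No exception is made for the washout.
- **Intervention:** "During the washout period, participants will not receive dietary recommendations".
- **Dietary and physical activity control:** two kinds of advice are described. One is an avoidance list: "Participants will be provided with a list of local foods to avoid due to their potential probiotic or prebiotic content". The other is lifestyle counselling: "Participants will receive nutritional counselling on a healthy Mediterranean diet providing approximately 25 kcal/kg/ day to achieve and maintain 7% loss of initial body weight". No time limit is given for the list.
- **Abstract, Methods/design:** the trial has "two intervention periods of 12 weeks separated by a washout period of 6 weeks and preceded by another washout period of 2 weeks", so the word washout covers both the lead-in and the gap between periods. Table 1 uses the label only for the gap between weeks 12 and 18.

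The primary outcome is the change in plasma LPS. Outcome measures and Table 1 place blood sampling at weeks 0, 12, 18 and 30, with stool also taken at weeks 0 and 18. Week 18 is therefore the period 2 baseline for LPS and microbiota.

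**The concern.** In ordinary language a list of foods to avoid is a dietary recommendation. Read at face value, one section keeps the list in force through the washout and another withdraws it. A site or participant cannot tell from the article which applies for those six weeks.

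The product under test is a probiotic, and the protocol's own Discussion treats diet as an important influence on the gut microbiota. Whether probiotic foods may be eaten just before week 18 affects what the washout can be said to have achieved, how the carryover assessment is read, and how comparable the two baselines are for the primary outcome. The ambiguity may also reach the lead-in, because the abstract calls that a washout too.

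**Working it through.** This is mainly a check of consistency. The arithmetic serves only to size the consequence.

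**1. Timeline.** The article gives 12 weeks of treatment, then "After a 6-week washout, participants will crossover to receive the alternative intervention for another 12 weeks". This gives 12 + 6 = week 18 and 18 + 12 = week 30, in agreement with Table 1.

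**2. The two readings of the washout sentence.**

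| Reading | Before week 0 | Before week 18 |
|---|---|---|
| (a) All dietary instruction is suspended, including the avoidance list | 2 weeks of restriction | 6 weeks without restriction |
| (b) Only the Mediterranean/weight-loss counselling is suspended | 2 weeks of restriction | Restriction continues |

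Under (a) the prebiotic/probiotic condition differs between baselines. Under (b) it is the same. Under either reading week 18 also follows a 12-week period of lifestyle intervention, which week 0 does not. The article does not say which reading is meant.

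**3. Effect of a shift on the treatment contrast.** Suppose reading (a) raises every week 18 value by s and leaves week 30 unchanged. Any part that persists to week 30 cancels from the change. Each period 2 change then moves by −s. Take each participant's difference, probiotic change minus placebo change:

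- probiotic first (n1 completers): period 1 change − period 2 change, which moves by +s;
- placebo first (n2 completers): period 2 change − period 1 change, which moves by −s.

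With no period term, the mean over all completers moves by s × (n1 − n2)/(n1 + n2). With a period term, the two sequence means are weighted equally and the movement is (s − s)/2 = 0.

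Inputs: 60 recruits at 1:1 give 30/30. The Sample size section's minimum of 21 per arm gives 21/21, if arm is read as sequence. The unequal splits are assumptions, since the document gives no completers by sequence.

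| Completers by sequence | Share of s entering the estimate, no period term |
|---|---|
| 30/30 or 21/21 | 0% |
| 27/30 | 3/57 = 5.3% |
| 25/30 | 5/55 = 9.1% |
| 21/27 | 6/48 = 12.5% |
| 21/30 | 9/51 = 17.6% |

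**4. Effect on precision.** With balanced sequences and no period term, half the differences move by +s and half by −s, which adds s² to their variance. If s were half the SD of the difference (an assumption), the variance would rise by 0.5² = 25%. A period term removes this common part. It does not remove extra scatter from participants eating different amounts of probiotic food.

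**The case against.** The strongest answer is that the passages can be reconciled. The avoidance list and the nutritional counselling are described separately, the list has no time limit, and the Study design rule has no exception. If dietary recommendations means only the counselling, the restriction runs through the washout. The abstract's usage gives some support: it calls the lead-in a washout, and the restriction applies in those same two weeks. This is a fair reading, and it means a reader may not infer that the two baselines are certainly taken under different prebiotic/probiotic conditions. It does not remove the need for clarification, because the article never limits the washout sentence in that way.

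A reader might also see a further contradiction in "In the following visits, an intensive lifestyle intervention programme will be carried out to reinforce the behaviour". There is none: Table 1 has no visit between weeks 12 and 18, so reinforcement at visits is compatible with silence during the washout.

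Nor does a week 18 shift by itself bias the treatment effect. Both sequences have the same washout instruction, so a common shift is a period effect. It does not in itself create the sequence difference that a carryover assessment looks for.

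Finally, the article condenses a fuller protocol that is not shown, and detailed participant instructions may stand there. That would excuse silence, but here two published statements conflict.

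**Conclusion.** The conflict stands as a conditional point. Study design and Intervention disagree on their face about diet from week 12 to week 18, and nothing settles whether the avoidance list applies. If it lapses, the week 18 baseline for LPS and stool is not comparable with week 0 in prebiotic/probiotic exposure, the washout is weaker, and a period effect and noise are added.

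A claim that the treatment estimate is biased would go too far. Bias needs both unequal completers and an analysis without period. It is then a fraction of s: zero at 30/30, about 5% at 27/30 and about 18% at 21/30, all for assumed splits and a shift that does not persist to week 30. The size of s cannot be derived from the document. The Statistical analysis section names treatment and time for the two-way ANOVA and does not list the factors of the three-way ANOVA used for carryover. Period may therefore be handled there or in an analysis plan not shown, and its absence from the article is not counted as an error.

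Making week 18 fully match week 0 is not a realistic aim, since week 18 comes after 12 weeks of lifestyle intervention whatever the washout rule.

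**What to change.** - Reconcile Study design and Intervention in one statement of which dietary instructions apply from week 12 to week 18, naming the avoidance list and the Mediterranean/weight-loss counselling separately. Say also whether the two-week lead-in, which the abstract calls a washout, is covered. The choice of rule belongs to the investigators. As the trial is described as ongoing, if instructions can no longer change, report what participants were actually told.
- Fit a period term in the LPS analysis, so that a common week 18 shift stays out of the treatment contrast whatever the split of completers.
- Use the week 18 three-day dietary record and FFQ, both already in Table 1, to flag prebiotic or probiotic intake before that baseline, and run a sensitivity analysis on it.

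The cost is a wording change and a small amount of extra analysis. No new data collection is needed.

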### Dietary and physical activity control

Participants will be provided with a list of local foods to avoid due to their potential probiotic or prebiotic content. Subjects will be asked to complete a three-day dietary record at the beginning, midpoint, and end of each intervention period. Energy and dietary intakes will be assessed from the 3-day records using the EvalFINUT software (http://www.finut.org/evalfinut/). Additionally, subjects will complete the Food Frequency Questionnaire (FFQ) at the beginning of each intervention period. Participants will receive nutritional counselling on a healthy Mediterranean diet providing approximately 25 kcal/kg/ day to achieve and maintain 7% loss of initial body weight and increase moderate-intensity physical activity (such as brisk walking) for at least 150 min/week following the guidelines of the American Diabetes Association for the prevention or delay of DM2 [15]. Likewise, physical activity will be monitored through the International Physical Activity Questionnaire (IPAQ) at the beginning, midpoint, and end of each intervention period. In the following visits, an intensive lifestyle intervention programme will be carried out to reinforce the behaviour.

